**Figure 2. f2:**
[figure not shown]
Overview of the study intervention in TIME-HF. RCT-Randomised Controlled Trial, DAOH-Days Alive and Out of Hospital, EHR-Electronic health record.

**
*Evaluate the scalability of proposed intervention model (Aim 3)*
**

*Cost effectiveness and acceptability analyses*

Information for economic analyses will be collected during the trial to obtain detailed resource consumption. A top-down approach will capture implementation costs from a health systems perspective by quantifying the resources deployed. Some of these will be once only activities (e.g., development of a mobile telephone application) but most will be recurring (e.g., nurse hours per year). We will then cost these resources according to unit costs in India. A bottom-up approach will collect patient level out of pocket expenditure and other personal financial losses or gains. It will include human resource costs, doctor visits, laboratory tests, cost of medications, and co-payments for medications. Rates of outpatient (specialty clinic) visits, hospitalisations, and clinical events will also be obtained. Indirect costs (travel, missed work time, and lost productivity) incurred by patients will be estimated using questionnaires that have been used in other South Asian studies
^
54
^.

We will collect qualitative data during the follow-up period. In depth interviews with patients, nurses and clinicians will be conducted to understand the adoption and acceptability of the intervention (
Table 4). Qualitative data collection approaches will be employed for prospective process measure evaluation during the trial. Process measures will include quality of care (patient centredness, safety, equity, access, and timeliness), and individual, organisational and system factors influencing effective roll-out of the intervention (causal mechanisms and contextual factors, further barriers and facilitators and motivators). The acceptability of the trial intervention among providers and patients, the feasibility of integrating and sustaining the program in the existing health care system will be also assessed. Additionally, by using a close-out questionnaire, we will also ask patients to self-report their compliance to individual elements of the intervention. Data from follow-up visits questionnaire will also capture key quality indicators (

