**Data analysis plan**

Aim1: All interviews conducted in local language (Malayalam) will be simultaneously translated to English and transcribed. Interviews conducted in English language will be transcribed. The data analysis will follow a framework method of analysis
^
55
^. After the data is transcribed, the transcripts will be read line-by-line to get familiarised with the data. First a few transcripts will be coded using an inductive method. Later, a working analytical framework will be generated by merging the initial codes. The working analytical framework will then be used to index the remaining interviews. After indexing all the interviews, key themes will be generated by merging categories having similar meaning for each stakeholder. Finally, the data will be interpreted based on the convergences and divergences between the data themes across different stakeholders.

 Aim 2: All quantitative analysis will follow guidelines of cluster randomised trials
^
56
^. We will employ intention to treat analysis except in the sub-group analyses. Initially, baseline characteristics will be compared by treatment group to examine the adequacy of randomisation. The primary analysis will be a complete case analysis. However, missing data on outcome variables will be reported and sensitivity analyses will be conducted after multiple imputation of missing data.

The DAOH will be calculated by subtracting days in hospital and days from death until end of study follow-up from the total follow-up time of 730 days. The DAOH is a patient-centred outcome, which accounts for multiple events over the two-year course of a study period, weighs death more than hospitalisation, and deaths occurring early more than those occurring later. Empirical density curves will be created to show the distribution of DAOH over two-year follow-up period, stratified by intervention group. The median and the interquartile range of DAOH by treatment group will be provided. Poisson regression with a robust variance estimate
^
57
^ and an offset term to account for clustering will be employed in the analyses of DAOH per two-years of follow-up time. This procedure will yield a rate ratio and 95% CI
^
57
^. The rate ratio is the DAOH in the intervention arm divided by DAOH in the enhanced usual care arm. A rate ratio of >1 indicates more DAOH in the intervention arm in comparison to the usual care arm (i.e., favours the intervention).

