The data on costs for the intervention and control groups will be compared to assess Incremental Cost-Effectiveness Ratios (ICER), the differences in outcomes between the intervention and control groups versus differences in costs of the intervention components. ICER measures will include the cost per case of primary outcome avoided. If the primary clinical outcomes are shown to differ significantly between group, a full economic evaluation of the lifetime costs, benefits, and cost-effectiveness (in life years gained) comparing the usual care to intervention strategy will be performed. Decision models from health system and societal perspectives, a lifetime analytic horizon, and 3% discounting of future costs and outcomes will be used. QALYs will be derived from EQ5D-VAS. We will also estimate the economic rate of return of an additional rupee spent on the intervention, with the return being in the form of knock-on costs of health services saved. For this purpose, the costs of the intervention will be the direct and indirect costs for the intervention components but excluding knock-on costs on health service use. The differences in the costs of health service use in the treatment and control participants will be used to construct an estimate of monetary savings. The ratio of these (discounted using 3%) savings and intervention costs, will be used to derive the economic rate of return over 2-years from the start of the intervention.

Aim3: All interviews conducted in local language (Malayalam) will be simultaneously translated to English and then transcribed by the post-doctoral and doctoral level fellows engaged in the study. Interviews conducted in English language will be transcribed. Field notes will be collected as part of process evaluation. Qualitative analysis will be done using a thematic analysis. A deductive coding approach will be done using the Normalisation Process Theory (NPT)
^
60
^, which will help to determine factors that promote or inhibit the incorporation of interventions into routine work. The findings will be interpreted using components of the RE-AIM
^
61
^ (Reach, Efficacy, Adoption, Implementation and Maintenance) framework to help inform the adoption, likelihood of adoption and key predictors of integrating and continuing the new care model.

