**Study outcomes**

Primary outcome is the days alive and out of hospital (DAOH) during the two-year follow-up period. Major secondary outcomes include; a) a composite endpoint of mortality (all-cause) or hospitalisation (>24 hours) during study follow-up period, b) six minutes walking distance, c) adherence to GDMT and d) quality of life.

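### The economic analysis names an ICER that cannot be computed for DAOH and takes QALYs from the EQ VAS; its cost term and its significance condition also need correcting

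*Protocol article*

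**What the plan says.** The economic methods are in one paragraph of the Data analysis plan. It describes the ICER as "the differences in outcomes between the intervention and control groups versus differences in costs of the intervention components" and adds that "ICER measures will include the cost per case of primary outcome avoided". A further step is conditional: "If the primary clinical outcomes are shown to differ significantly between group, a full economic evaluation of the lifetime costs, benefits, and cost-effectiveness" is to follow, with life years gained as its unit, health system and societal perspectives, and a lifetime horizon. The next statement on units is that "QALYs will be derived from EQ5D-VAS".

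The paragraph ends with a two-year economic rate of return. For that measure alone, "the costs of the intervention will be the direct and indirect costs for the intervention components but excluding knock-on costs on health service use"; differences in health service costs enter it as savings.

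Elsewhere, Study outcomes states: "Primary outcome is the days alive and out of hospital (DAOH) during the two-year follow-up period". The Data analysis plan gives its direction: "A rate ratio of >1 indicates more DAOH in the intervention arm in comparison to the usual care arm". The section on cost-effectiveness and acceptability under Aim 3 lists patient-level out-of-pocket spending and says that "Rates of outpatient (specialty clinic) visits, hospitalisations, and clinical events will also be obtained". Table 3 schedules the EQ-5D-5L at baseline and at each of the eight three-monthly visits. Aim 3(a) in the Introduction, and the Discussion, promise an assessment of overall cost-effectiveness with no condition attached.

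**The concern.** Cost-effectiveness is a stated aim, and the article fixes how it will be measured. Four things in that specification look wrong.

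- The only unit named for the trial-based ICER belongs to a binary adverse event, not to a count of good days.
- The QALY weight comes from a rating of one's own health, which does not express a preference between length and quality of life and is not anchored at dead = 0.
- As worded, the ICER cost term covers the intervention package. The Discussion and its Implications section expect the intervention to prevent hospital admissions, so savings or added costs in health-service use are central to the ratio.
- The lifetime evaluation depends on a significance test of the clinical outcome. Cost-effectiveness depends on costs and effects jointly, and an unclear clinical gain with lower costs can still matter to a payer.

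If these stand, the trial could finish with complete economic data and no interpretable ratio by the definitions it published.

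**Working it through.** **1. ICER unit.** A ratio per case avoided needs a number of cases in each arm. DAOH is 730 days minus days in hospital and days lost to death, so each patient contributes a number of days. The planning values are 586 and 566 days, and the effect is 586 - 566 = 20 days gained. No case count can be formed. The ratio that matches the outcome is (mean cost, intervention - mean cost, usual care) / (mean DAOH, intervention - mean DAOH, usual care), in rupees per additional day. The composite of death or hospitalisation would give cases to avoid, but Study outcomes lists it as secondary.

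**2. QALY source.** The EQ VAS and the EQ-5D-5L index are different quantities; only the index comes from a preference value set with dead = 0. The documents give no VAS or index means, so the error cannot be sized. As illustration only, assume a mean VAS of 0.6. With an index of 0.5, QALYs from added survival would be 0.6/0.5 - 1 = +20% off; with an index of 0.8, 0.6/0.8 - 1 = -25%. Even the sign is unknown. The paragraph also gives life years gained as the unit of the full evaluation and then introduces QALYs without saying which governs.

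**3. Cost term.** The ICER sentence refers to costs of the intervention components. The explicit exclusion of knock-on costs is written for the rate of return. Hospitalisation, outpatient and out-of-pocket data are collected for the economic analyses, but the only calculation that expressly uses the difference in health-service costs is the rate of return. Whether the ICER includes them is left open by its own wording.

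**4. Significance condition.** Inputs from Trial sample size and power: difference 20 days, SD 69, 770 per arm, two-sided 5%, ICC 0.01, stated design effect (DE) 2.08, CV of cluster size 0.85. Study coordination gives 70 patients per centre.

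- Standard error = SD × √(2 × DE / n) = 69 × √(2 × 2.08 / 770) = 5.07 days.
- Power ≈ Φ(20/5.07 - 1.96) = Φ(1.98) = 97.6%.
- With DE from the stated CV, 1 + ((0.85² + 1) × 70 - 1) × 0.01 = 2.20: standard error 5.21, power 97.0%.
- With a t distribution on 20 df the two figures are 96.3% and 95.4%.

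The stated 91% is not reproduced; it would need a DE of about 2.97. That is a separate matter. For a true effect of 20 days, the chance that the lifetime model is skipped is 1 - power: about 2-3% (4-5% with the t version), or 9% at the stated power.

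Smaller true effects are assumptions. With SD 69 and DE 2.08 to 2.20:

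| True gain (days) | Chance the lifetime model is run | Mean estimated gain when it is run (days) |
|---|---|---|
| 20 | 97-98% | 20.3-20.4 |
| 15 | 82-84% | 16.5-16.7 |
| 10 | 48-51% | 14.0-14.3 |
| 5 | 16-17% | 12.4-12.7 |

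A lifetime model run only after significance therefore starts from an inflated effect when the true effect is small: about 14 days on average if the truth is 10.

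**The case against.** Five points can be made on the other side.

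- **The unit may be loose drafting.** The Abstract also mentions overall survival and the economic paragraph speaks of primary outcomes in the plural, so a death avoided may have been meant. But Study outcomes names DAOH alone, and the sentence refers to the primary outcome.
- **The VAS may be a slip for the EQ-5D-5L.** Possibly, but the sentence is explicit, and correcting it costs a few words.
- **The cost phrase is not a firm exclusion.** This largely stands. A reader might infer that hospital costs are ruled out of the ICER. The same sentence opens by comparing cost data between the groups, the relevant data are collected, and the exclusion of knock-on costs is confined to the rate of return. The lifetime model could also include them. The documents support a finding of ambiguity, not of omission.
- **The condition is narrower than it looks.** This stands too. A reader might infer that a non-significant result leaves cost-effectiveness unanswered. The condition covers only the lifetime evaluation; the trial ICER and the two-year rate of return are unconditional. Whether to build a lifetime model after a null trial is partly a question of scope.
- **A condensed article may leave detail to a fuller plan.** It may, so the absence of methods for uncertainty is no fault. The unit and the QALY source are different: they are stated, and stated wrongly.

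A reader might also argue that the condition will usually fail, because DAOH will vary far more than 69 days. The Introduction's mortality figures, under simple assumptions, can be turned into SDs of 215 to 238 days, giving power of 21-24% and a skipped model in 76-79% of trials. No section states such an SD for DAOH, and the figure requires this trial's mortality to resemble those sources, so it is not relied on here.

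**Conclusion.** The point holds in limited form. Two errors are certain from the text: the trial ICER is given a unit that DAOH cannot supply, and the QALY weight is taken from a scale that is not preference-based. Two further points are real but smaller. The ICER cost term is ambiguous about health-service use. The significance condition on the lifetime evaluation conflicts with an aim stated without condition, and it favours overestimates when the true effect is small.

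The documents give no costs, utilities or willingness-to-pay threshold, so the effect on any cost-effectiveness result cannot be computed. The skip probabilities of 2-3% and 9% assume a true effect of 20 days and SD 69; the table's other rows assume smaller effects. The VAS percentages are illustrations. Confidence is high on the unit and the QALY source. The primary efficacy analysis is untouched; the correction should be made because a stated aim depends on it.

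**What to change.** Amend the economic paragraph of the Data analysis plan as follows.

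1. Replace the per-case ratio with incremental cost per additional day alive and out of hospital, and per QALY gained.
2. Derive QALYs from EQ-5D-5L index values with a published value set and death valued at 0, using the nine scheduled assessments. State whether the full evaluation reports life years, QALYs or both.
3. Define the ICER numerator as the difference in total cost between arms, including health-service use as well as the intervention. Keep the narrower cost definition for the rate of return only.
4. Remove the significance condition from the lifetime evaluation.

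Items 1 to 3 are changes of wording with modest extra analysis, and use data already being collected. Item 4 costs some modelling work after a null result. All four should be settled before outcome data are compared by arm.

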**Study outcomes**

Primary outcome is the days alive and out of hospital (DAOH) during the two-year follow-up period. Major secondary outcomes include; a) a composite endpoint of mortality (all-cause) or hospitalisation (>24 hours) during study follow-up period, b) six minutes walking distance, c) adherence to GDMT and d) quality of life.

**Data safety and monitoring**

The central team will review the data on real-time basis and feedback will be provided to the participating sites. Periodic monitoring of the data will be done once in six months. Source data verification of 10 percent of the data fields will be conducted. A data safety monitoring board (DSMB)
^
62
^ with members independent of the trial will review the trial outcome and data safety annually.

## Discussion

Heart failure is a chronic condition with a wide range of effects on the activities of daily living and require lifelong management. There have been considerable advancements in the treatment and management of HF in the recent past. Despite these developments, HF patients still experience high treatment burden, reduced quality of life, frequent hospitalisations, and death
^
63
^. A team-based approach involving task sharing with different cadres of health care providers may be best suited for management of a multimorbid condition like HF in Indian settings.

Guideline directed medical treatment is the main pillar of chronic management of HF with reduced EF
^
64,
65
^. One of the challenges in HF management is the implementation of complex treatment regimens especially for those with co-morbidities and the effective tracking of patients to monitor the disease progression. A patient who has been initiated on GDMT needs careful monitoring and close follow-up for titration of the medication. Although the benefits of GDMT in the management of HF have been documented, there exists a gap in the provisioning and the adherence of GDMT
^
66
^. At the patient level, the requirement of frequent travel to the clinic to manage their conditions is a barrier and an important limiting factor in ensuring continuity of care. Strategies to improve adherence to GDMT should therefore explore patient related barriers and address them effectively.

Timely monitoring of the symptoms of congestion and the effective implementation of healthy behaviours into the daily lives are additional challenges in HF management
^
67
^. Given the effectiveness of the task sharing strategy of enabling nurses in management of cardiovascular conditions
^
17,
18
^, monitoring patients remotely with a specially trained nurse, and nurses acting as care coordinator in a team-based care model with support from physicians and other health care providers are viable strategies to improve HF outcomes in low resource settings.

The mHealth application facilitates real time monitoring of the warning signs and symptoms of worsening HF. The patients will be advised to update risk factors, anxiety levels, depression, warning signs and symptoms of HF through the mHealth application. In addition to the daily monitoring of the patients, they are also advised to report a weekly survey. This can help the nurses and the doctor to make informed and timely decisions on management of the patients and prevent the need for hospitalisation due to exacerbations or worsening of the condition.

Although CCM has been a successful model in high-income settings for management of chronic conditions, there is still a lack of understanding on the acceptability, and feasibility of this model among patients and providers in India and other LMICs
^
68
^. Our trial will explore the acceptability and feasibility of CCM the Indian settings. We will also investigate the overall cost-effectiveness of the intervention strategy. The effect of CCM on mental health conditions like depression and anxiety is promising
^
69,
70
^. Since HF is a multimorbid condition and often co-exists with mental health conditions, CCM may have important role in improving the quality of life, and physical functions of the patients compared to routine care. In our trial, the CCM will be developed based on the inputs from various stakeholders like doctors, nurses, patients, and their caregivers. This will help us to design a contextually relevant and patient centred approach in management of HF.

### Implications

The findings of TIME-HF trial will have the potential for changing the care delivery of HF and other chronic conditions in India. The knowledge generated from TIME-HF study will identify the system-level changes needed to address the limitation of the current care for HF. The collaborative care model has the potential to improve the communication and collaboration between specialists, nurses, and other stakeholders for a comprehensive care delivery for HF. The remote monitoring, early identification of the warning signs and symptoms of worsening of disease conditions, and timely management may help to prevent hospitalisation and mortality in HF patients.

### Dissemination

The key-findings will be published in leading academic journals as well as it will be presented in conferences. Policy implication of the study findings will be developed, and it will be shared with various stakeholders at the state, regional and national level.

### Study status

At the time of protocol submission, all participating sites had been identified and recruitment of patients started. The data collection is planned to be completed by 2025.

## Data Availability

No data are associated with this article. Figshare: Structured Questionnaire https://doi.org/10.6084/m9.figshare.21802917.v1
^
38
^ The file “Structured Questionnaire” contains the following extended data: Baseline Proforma 3
^rd^, 6
^th^, 9
^th^, 12
^th^, 15
^th^, 18
^th^, 21
^st^, 24
^th^ month follow-up questionnaire Figshare: 7
^th^ day Follow-up Questionnaire https://doi.org/10.6084/m9.figshare.21802815.v2
^
39
^ The file “7
^th^ day Follow-up Questionnaire” contains the following extended data 7
^th^ day follow-up questionnaire for intervention arm only Figshare: Informed Consent (TIME-HF study) https://doi.org/10.6084/m9.figshare.22360375.v1
^
30
^ The file “Informed Consent (TIME-HF study)” contains the following extended data Participant information sheet and Consent form Figshare: List of participating centres https://doi.org/10.6084/m9.figshare.22360585
^
36
^ Figshare: Data Safety Monitoring Board https://doi.org/10.6084/m9.figshare.22360561
^
62
^ Figshare: Timeline of TIME-HF trial https://doi.org/10.6084/m9.figshare.22360615
^
33
^ Data are available under the terms of the Creative Commons Attribution 4.0 International license (CC-BY 4.0).
